**Figure 1 Fig1:**
[figure not shown]
**Flow diagram of the randomized clinical trial.**

### Randomization and allocation concealment

A randomization sequence will be created using a computer-generated list of random numbers in block sizes of two. The randomization will be computer generated using Proc Plan, SAS® software Version 9.1.3 (SAS Institute Inc., Cary, NC, USA). Patients will be allocated to one of two interventions: cycle ergometer and conventional exercises (group I) or conventional exercises alone (group II). All participants will have the same probability of inclusion in either group. The allocation sequence will be concealed in sequentially numbered opaque, sealed envelopes. The envelopes with the random sequence will be in the possession of a person not involved in the trial. Envelopes will be opened only after the enrolled patients have completed all baseline assessments.

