## Methods/Design

### Study design

The study is a prospective, parallel-group, single center, randomized pilot study conducted in accordance with Consolidated Standards of Reporting Trials (CONSORT) guidelines [14].

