### Blinding

Because of the nature of the interventions, patients and intervention applicator (principal investigator) will not be blinded. However, there will be blinding of data collectors responsible for baseline and follow-up assessments, and these physiotherapists will be trained to apply the assessment tools used to collect data for statistical analysis and interpretation of outcomes. For blinding to be maintained the data collectors will not have contact with participants during the intervention and the follow-up. The contact is only at the time of evaluation outcomes measures. The physiotherapy sessions will be conducted individually, in schedules that do not coincide with the presence of the physiotherapist data collector or other participant.

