Thus, the resources employed in physical therapy, which have been used and investigated frequently in adults, should be better understood when applied to older patients. The cycle ergometer activates the muscle groups of the hip, knee, and ankle; favors the increase and maintenance of joint ROM of the lower limbs and requires motor coordination for the execution of movements [32]. Liebs *et al*. [13] evaluated the effects of cycle ergometer-associated exercises in patients with THA and TKA in the early postoperative period. Patients performed cycle ergometer-associated exercises 3 times per week for 3 weeks. In patients with THA, pain and function, as assessed by the WOMAC, were found to be improved 3 months postoperatively in the group that performed cycle ergometer-associated exercises compared with patients who received only conventional physical therapy. No significant improvements were observed in patients with TKA.

The sessions will be supervised by the same physiotherapist and all exercises individualized, with progression guided by the patient’s function and pain level. Blood pressure and heart rate will be noted at the beginning and end of the session as well as before, during and after cycle ergometer-associated exercise.

Primary outcome measures include two instruments: the HHS for functional evaluation of the hip and the SPPB for evaluation of performance of the lower limbs. The inclusion of the HHS was justified by its frequent use in the local orthopedic community for functional hip assessments in addition to its recommendations in the literature and evidence of validity and reproducibility for patients undergoing THA [17]. These authors emphasize that this assessment system is the most widely used in the evaluation of hip arthroplasty [17]. The SPPB is an effective tool for evaluating the physical performance of the lower limbs in the older population and has been used in research on aging because of its high sensitivity in identifying changes in functionality [33,34].

The secondary outcome measures used in this trial are patient-reported outcome measures broadly applied in interventional and observational studies in patients with THA [8,10,12,13]. Recommendations that both generic and specific measures be included in the assessment of HRQOL can be found in the literature [35,36].

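### Fixed blocks of two, with one unblinded therapist who sees every allocation, make every second allocation predictable and put the pilot's effect size at risk of selection bias

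*Protocol article*

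**What the plan says.** The section Randomization and allocation concealment specifies a "computer-generated list of random numbers in block sizes of two" and adds: "All participants will have the same probability of inclusion in either group". Study design describes a "prospective, parallel-group, single center, randomized pilot study", and no stratification is described anywhere. There is therefore one running sequence in which every block holds one patient of each group.

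Three safeguards are described in the randomisation section:
- The form of concealment: "The allocation sequence will be concealed in sequentially numbered opaque, sealed envelopes".
- Custody: someone outside the trial keeps them.
- The moment of opening, which comes once baseline is finished: "Envelopes will be opened only after the enrolled patients have completed all baseline assessments".

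Under Blinding, "patients and intervention applicator (principal investigator) will not be blinded"; the assessors are blinded. The Discussion adds: "The sessions will be supervised by the same physiotherapist". Read together, these statements mean that one person, the principal investigator, delivers both interventions and learns each allocation as it occurs. The article does not describe varying the block size or withholding it from anyone.

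**The concern.** A 1:1 block of two has only two possible orders, I-II and II-I. Anyone who knows the block size and has seen the first allocation of a pair knows the second before its envelope is opened. Envelopes and an outside holder hide the physical list, but they cannot hide an allocation implied by the one before it.

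If the person with that knowledge can influence who enters, or in what order, patients with better or worse prospects can drift towards one arm, deliberately or not. Blinded assessment does not correct this, because it protects measurement and not entry. At stake is the between-arm effect size, which Objectives and hypotheses says will be used to calculate the sample size of the full trial.

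**Working it through.** The article gives no predictability figure and no sample size, so there is no stated figure to reproduce.

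**Inputs.** Block size 2 and equal allocation (Randomization and allocation concealment); one centre and no strata (Study design); one unblinded therapist who sees all allocations (Blinding; Discussion). Assumption: this person knows the block size. The article states it and does not say that it is withheld.

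**Step 1: predictability of fixed blocks.** For a block of 2b patients whose size is known:
- share of allocations known with certainty = 1/(b + 1)
- expected correct guesses per block, naming the arm with more places left = b + (2^(2b)/C(2b,b) − 1)/2

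For b = 1, the certain share is 1/2 = 50%. Correct guesses are 1 + (4/2 − 1)/2 = 1.5 of 2, or 75%. Full enumeration of the sequences gives the same values.

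**Step 2: alternatives.** The varying-block rows are simulated (4,000 runs, assumed 40 allocations) for a guesser who knows the possible sizes but not the one in use.

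| Scheme | Certain | Guessed correctly |
|---|---|---|
| Fixed 2 (protocol) | 50% | 75% |
| Fixed 4 | 33.3% | 70.8% |
| Fixed 6 | 25.0% | 68.3% |
| Fixed 8 | 20.0% | 66.6% |
| Varying 4/6 | about 5.7% | 68.9% |
| Varying 4/6/8 | about 2.4% | 67.6% |
| Simple randomisation | 0% | 50% |

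**Step 3: possible bias.** Suppose patients entered when group I is expected differ by +h SD in the analysed outcome, and by −h SD when group II is expected. With a proportion p of correct guesses, the arm difference is biased by 2h(2p − 1).
- Blocks of two: 2h(2 × 0.75 − 1) = h.
- Varying 4/6/8, steering on every guess: 2h(2 × 0.676 − 1) = about 0.70h.
- Varying 4/6/8, steering only when the allocation is certain: 2h × 0.024 = about 0.05h. The same rule for blocks of two gives 2h × 0.50 = h.

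The documents give no value for h. As an illustration, h = 0.25 gives a bias of 0.25 SD under blocks of two, which equals the delta that Statistical analysis labels small. Under varying 4/6/8 blocks it gives about 0.01 to 0.18 SD.

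**Step 4: when foreknowledge can act.** Participants and recruitment procedures places the invitation before discharge, and baseline at the first therapy session, 2 weeks after surgery. Envelopes are opened only after baseline. A patient's place in the sequence is thus settled up to about two weeks after invitation. What remains open to influence is the late judgement on ability to attend sessions (an exclusion criterion in Table 1) and the order of first sessions. Invitation itself is exposed only if patients arrive further apart than this lag, and no accrual rate is given.

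**The case against.** A reader might infer that concealment has failed outright, and that every even-numbered allocation is known before that patient is invited or consents. The documents do not support this. The article does not say who screens, invites or schedules; the principal investigator is neither named nor ruled out. Because invitation precedes allocation, a second-position patient may already have been invited before the partner is randomised. The first patient of each pair remains concealed throughout.

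The article also limits the room for steering. Recruitment is consecutive, most criteria in Table 1 are objective, and Feasibility outcomes has refusals, withdrawals and dropouts recorded. These measures restrict steering or make it visible, but do not exclude it.

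The modelled bias rests on an h with no source in the article. The primary clinical outcome is a mean change, so a difference in baseline level need not carry over one for one.

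Finally, this is a pilot whose main purpose is feasibility. Of its four aims, only the effect-size aim depends on the comparison between arms, so it would be wrong to infer that the whole pilot is compromised.

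All of this stands and limits the point to a risk. None of it hides the second allocation of a pair from someone who has seen the first.

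**Conclusion.** The point holds as a risk of selection bias. With the stated block size and one unblinded therapist seeing all allocations, 50% of allocations are certain in advance and 75% can be guessed, against 50% guessable under simple randomisation. These figures are exact, provided that the therapist knows the block size.

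Whether bias follows depends on that person's influence over late eligibility judgements or the order of first sessions, and over invitation if accrual is slow. The article leaves this open, so neither the occurrence nor the size of any bias can be established from it. What is exposed is the effect size intended for planning the full trial. Recruitment, retention, tolerability and feasibility of the outcome measures are not affected.

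**What to change.** **Unopened envelopes.** Replace the block size of two with a new computer-generated list using larger, randomly varying block sizes (for example 4, 6 and 8), not disclosed to the principal investigator or recruiting staff. Certain allocations fall from 50% to about 2%, but correct guesses only from 75% to about 68%. It therefore also helps if those who enrol and schedule patients do not know past allocations. The cost is one new list and one new envelope set. The new list can leave the arms at most 4 apart.

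Simple randomisation removes predictability entirely, but the arms may then differ by more than 4. For assumed totals of 20 to 60 patients, the probability of this is about 26% to 52%.

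**Patients already randomised in pairs.** Trial status gives a start in August 2011 and about two years of recruitment, so few envelopes may remain and these steps may matter more:
- Compare baseline HHS and SPPB between arms within the second positions. Under the model above, a baseline shift of h would show there as a gap of 2h. Comparing second with first positions would not reveal it, because +h and −h average to zero. In a small pilot, finding no gap is only weak reassurance.
- Add a sensitivity analysis of the arm difference limited to the first patient of each pair, whose allocation could not be foreseen. It halves the sample, so it should be reported as an estimate with its interval.

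Both steps use data already collected, plus the order of randomisation.

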### Blinding

Because of the nature of the interventions, patients and intervention applicator (principal investigator) will not be blinded. However, there will be blinding of data collectors responsible for baseline and follow-up assessments, and these physiotherapists will be trained to apply the assessment tools used to collect data for statistical analysis and interpretation of outcomes. For blinding to be maintained the data collectors will not have contact with participants during the intervention and the follow-up. The contact is only at the time of evaluation outcomes measures. The physiotherapy sessions will be conducted individually, in schedules that do not coincide with the presence of the physiotherapist data collector or other participant.

### Interventions

All subjects will receive the same clinical and orthopedic care during hospitalization; that is guidelines for positioning in bed, transfers, limitations of range of motion (ROM) (hip flexion ≤ 90 degrees and hip adduction only to midline) and adaptations in the home (raising the heights of the toilet, bed, sofa, and chairs if necessary).

All subjects will receive a conventional-exercises program. Conventional-exercise sessions will last 50 minutes and be performed 2 days a week for 8 weeks. At the end of the intervention, patients will have performed 16 sessions and will be 10 weeks postoperative.

Under the guidance of a physical therapist, group I will perform cycle ergometer exercises on a vertical, stationary cycle ergometer, Dyamond line, Uniforce Fitness, Dy, model EB 497E ([contact]) (Figure 2) and conventional exercises and group II will perform conventional exercises alone. Ergometer resistance will be minimal (30 W) because the aim is not to perform cardiac exercise. The duration of ergometer cycling will be increased gradually, starting with 10 minutes in the first 2 sessions and increasing to 20 minutes for the remainder, and its aims are to improve coordination, proprioception, ROM, and muscle strength. For this reason, changes are not made during performance of the exercise; frequency is maintained at 60 revolutions per minute and the resistance is also maintained at the starting level. The height of the saddle will be set so that the forefoot will reach the pedal with the knee in minimum flexion (5 to 10 degrees). Special attention will be given to monitoring heart rate and blood pressure before, during, and after exercise. Patients will be instructed to follow the exercises on the cycle ergometer under the supervision of a physiotherapist, ensuring the execution of this only in the presence of the professional.

**Figure 2 Fig2:**
[figure not shown]
**Photograph of the cycle ergometer.**

Conventional exercises will consist of exercises to improve joint ROM, muscle strength, function, balance, coordination and gait. A description of conventional exercises is provided in Table 2.

**Table 2 Tab2:** **Description of conventional exercises used in total hip arthroplasty rehabilitation**

**Weeks postoperative**	**Lower-limb weight-bearing/Assistive device for walking**	**Description**
2 to 4	Partial/Walker	• Stretching (30 seconds each muscle group): hip flexors, extensors, adductors; knee flexors, extensors; ankle dorsiflexors and plantar flexors
		• Active assisted range of motion (5 to 10 repetitions): hip flexion, extension, abduction, external rotation; knee flexion, extension
		• Muscle strengthening (1 to 3 sets of 10 to 15 repetitions):
		o Hip flexors, extensors, abductors (low-resistance rubber band fixed to the ankle in standing position)
		o Knee extensors (sandbag fixed to the ankle in a seated position)
		• Transfer training: supine to side - lying in bed; sit and stand bed and chair
		• Gait training using a parallel bar and assistive device
4 to 6	Total/Crutch or cane	• Stretching maintained
		• Active range of motion (5 to10 repetitions): hip flexion, extension, abduction, external rotation; knee flexion, extension
		• Muscle strengthening (1 to 3 sets of 10 to 15 repetitions):
		o hip flexors (moderate-resistance rubber band fixed to the ankle in standing position)
		o hip abductors (standing position and seated position with moderate-resistance rubber band)
		o hip extensors (bridge exercise, one- and two-footed in supine position)
		o knee extensors and flexors (weight-training equipment, in a seated position, 20% 1RM)
		• Balance and gait training: walking on an unstable surface, backward walking, side step with the use of parallel bars if necessary
6 to 8	Total/With or without cane	• Stretching maintained
		• Muscle strengthening (1 to 3 sets of 10 to 15 repetitions):
		o hip flexors and abductors maintained
		o hip extensors (bridge exercise, one- and two-footed in supine position with ball)
		• Climbing and descending stairs
		• Coordination, balance, and gait training: circuits with stairs, obstacles, changing direction, changing speed
8 to 10	Total	• All exercises maintained
		• Addition of the muscle strengthening of hip and knee extensors with squat exercises (1 to 3 sets of 10 to 15 repetitions)

RM, repetition maximum.

Description of conventional exercises used in total hip arthroplasty rehabilitation.

### Intervention and follow-up periods

Assessments will be made at baseline (2 weeks postoperatively), after intervention (10 weeks postoperatively) and at 6-month follow-up (24 weeks postoperatively), and both treatment groups will have completed the intervention after 10 weeks. After the 10 weeks of supervised intervention, patients will be advised to perform some exercises unsupervised at home. In the period between the end of supervised intervention and the final evaluation (at 24 weeks), patients will be able to telephone the physiotherapist for assistance, and there will be a phone contact in the 18th week postoperatively to assess the patients' health condition.

### Outcome measures

At baseline, an instrument for sociodemographic and clinical characterization will be used to obtain data regarding age, sex, race, marital status, education, weight, height, body mass index, comorbidities, medications, joint pain, and lifestyle. Data regarding THA surgery outcome, the primary clinical outcome, will be the mean change in the hip function and physical performance of the lower limbs. The instruments used will be: Harris Hip Score (HHS) [15] and the Short Physical Performance Battery (SPPB) [16]. The mean change in total score in these instruments between the 2 arms, as measured at baseline, 10 and postoperative weeks postoperative will be the primary outcome measure. We will also collect: reason for surgery, waiting time to perform the surgery prosthesis fixation, affected side, hospital stay, postoperative complications, availability of a caregiver after surgery, adaptations at home, and satisfaction with the results of surgery and rehabilitation.

### Primary outcome measures

The feasibility outcome will include an evaluation of eligibility, recruitment and retention rates (in line with CONSORT recommendations), as well as monitoring of completion of outcome measures and assessments. The primary clinical outcome will be the mean change in the hip function and physical performance of the lower limbs. The instruments used will be: the HHS [15] and the SPPB [16]. The mean change in total score in these instruments between the 2 arms, as measured at baseline, 10 and 24 postoperative weeks will be the primary outcome measure.

The HHS questionnaire, an instrument that was developed to evaluate the results of THA, has been validated abroad [17] and in Brazil [18]. It consists of a scale ranging from 0 to 100 points in 4 domains: pain, function, deformity, and ROM. The maximum scores are 44 points for the pain domain and 47 for the functional domain, the latter being subdivided into activities of daily living (14 points) and gait (33 points). Domains are scored based on subjects’ responses obtained through interviews, with the exception of the deformity and ROM domains, which are evaluated by the examiner with the use of a tape measure and goniometer. The deformity domain can be scored from 0 to 4 and the ROM domain from 0 to 5, with higher scores indicating greater ROM, but within of limits for prosthesis, and less deformity. It is considered a poor functional outcome if the HHS total score is less than 70 points, fair if the score is between 70 and 79; good if the score is between 80 and 89, and excellent for 90 to 100 points [15,18].

The SPPB comprises tasks that assess balance, gait speed, and lower-limb strength in older people. It was developed in 1994 by Guralnik *et al*., with support from the National Institute on Aging, for the Established Populations for Epidemiologic Studies of the Elderly project in the US [16]. It is an effective tool for evaluating the physical performance of the lower limbs in the older population and consists of three tests that evaluate, in sequence, static standing balance; gait speed at a normal pace; and, indirectly, muscle strength in the lower limbs through the motion of getting up from a chair and sitting down again five consecutive times without the aid of the upper limbs. Each test is scored on a scale ranging from 0 (poor performance) to 4 points (optimal performance). The SPPB total score is obtained by adding the scores for each test and ranges from 0 (poor performance) to 12 points (best performance) [16,19]. The results may be interpreted as inability or very poor performance (0 to 3 points), low performance (4 to 6 points), moderate performance (7 to 9 points) and high performance (10 to 12 points) [20-22].

### Secondary outcome measures

HRQOL will be considered a secondary outcome and the questionnaires used to assess this will be the Medical Outcomes Study 36-Item Short-Form Health Survey (SF-36) [23] as a generic instrument and the Western Ontario and McMaster Universities Osteoarthritis Index (WOMAC) [24] as a specific instrument (measured at the same time points).

The SF-36 is a generic tool for assessing HRQOL that has been translated and validated in Brazil [25]. It consists of 36 items comprising 8 categories: functional capacity (10 items), physical aspects (4 items), pain (2 items), general health status (5 items), vitality (4 items), social aspects (2 items), mental health (5 items) and a question comparing current health conditions with those from a year ago. Each question is assigned a score and the scores tabulated and normalized to a scale of 0 to 100, where 0 corresponds to worst health status and 100 to best health status. There are no cutoff points, and each category is evaluated separately [23,25].

The WOMAC is a specific instrument that measures quality of life in patients with OA of the hip and knee [24]. Its use is indicated for postoperative evaluation of total arthroplasty of the knee (TKA) or hip [26]. The questionnaire was originally intended to be self-administered; however, it has been used for telephone interviews, and recently a computer touch-screen version has been validated. It comprises 24 items divided into 3 categories. The pain category has five questions, the joint stiffness category two questions, and the physical disability category seventeen questions. Each question has five possible answers using a Likert scale representing difficulty, and the responses *none* or *never*, *mild* or *monthly*, *moderate* or *weekly, severe* or *daily*, and *extreme* or *always* correspond to scores of 0, 1, 2, 3 and 4, respectively. Thus, 0 represents the absence of the symptom and 4 the worst manifestation of that symptom. Summing the scores, each category receives a score that is normalized to a scale of 0 to 100 points, with 0 representing the best health status and 100 the worst possible status [24,27].

